### Sample size

A conservative estimate of the primary outcome of hypoxaemia is set at 16%, following an unpublished 2016 audit of data from the Queensland Children’s Hospital, which we found was comparable to a published report [1]. Assuming a clinically relevant effect size of a 50% reduction in the proportion of desaturation events from 16 to 8%, along with a type I error of 0.025 (adjusting for two primary outcomes using Bonferroni’s correction) and power of 90%, 816 intubation encounters in total are required. Successful first-attempt intubation, the second primary outcome, assumes an absolute increase from 60 to 80%, requiring 258 intubation encounters. Allowing for 15% attrition, the total sample size that will satisfy both primary outcome measures is 960 intubation encounters. An attrition rate of 15% was selected based on the assumption that a proportion of patients enrolled will have a clinical deterioration, or other clinical events, during a high-stress procedure leading to the inability to deliver the intervention or collect the outcome data required for the study.

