### Randomisation

A computer-generated randomisation sequence using block randomisation (block size = 10) with a 1:1 ratio and stratification by site, age (< 1 year, 1–7 years and > 7 years of age), then level of the intended first operator seniority (junior and senior medical officer) was developed. Randomisation is conducted using sequential, numbered, sealed, opaque envelopes, provided to each site. The use of a fixed block size is unlikely to reduce the allocation concealment as randomisation occurs by any member of the large clinical team, including when the research staff are not present outside of usual business hours. Thus, any person selecting the envelope is unlikely to be aware of the previous allocations in the block. After a patient has been screened and confirmed as eligible and the operator for the intubation has been determined, the enrolling clinician selects the next envelope to reveal the study randomisation for that intubation encounter.

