#### Analysis methods

##### Primary outcome measures

The primary outcome measures will be analysed using logistic regression adjusting for the treatment group and the stratification variables (age group, operator level) as fixed effects and site and patient as random effects (allowing for the same patient to be recruited more than once into the study). A model without adjustment for age group or operator level will also be reported. Unadjusted and adjusted odds ratios (ORs), 95% confidence intervals (CIs) and *p*-values for the adjusted model will be reported (Table 2). Assumptions of the models will be tested and reported on.

**Table 2 Tab2:** Intubation characteristics of participants enrolled in the Kids THRIVE trial

Characteristic	Standard care, *N* =	THRIVE, *N* =
**Intubation location,** *n (%)*		
Emergency department		
Paediatric intensive care		
Neonatal intensive care		
Others		

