#### Missing data

The primary outcome for this study is recorded by two methods, paper CRF and video recording, as such it is expected that there will be very few participants with missing primary outcome data. Where the data is not recorded on either the paper CRF or video, the medical record will be used to source the required data. As such, multiple imputation will only be undertaken if > 10% of the primary outcome data is unavailable and reported as sensitivity analysis. The fully conditional specification will be used for imputation; the imputation model will include randomised treatment arm, study site and the stratification variable. Ten sets of imputed data will be created using the methods described for the primary outcome. A pooled common effect estimate and 95% confidence interval will be generated from the imputed datasets.

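### The planned imputation model names no predictor beyond those already in the primary model, so it is expected to return the complete-case estimate and cannot reveal bias from missing outcomes

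*SAP article*

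**What the plan says.** The Missing data section makes multiple imputation conditional on more than 10% of primary outcome data being unavailable and reports it as a sensitivity analysis. The method is chained equations with ten imputed datasets. On the predictors, the section states that "the imputation model will include randomised treatment arm, study site and the stratification variable". No other predictor is named, and no analysis allows for data missing not at random.

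The Primary outcome measures section specifies "logistic regression adjusting for the treatment group and the stratification variables (age group, operator level) as fixed effects". Site and patient enter the same model as random effects. The Randomisation section gives the strata as "stratification by site, age (< 1 year, 1–7 years and > 7 years of age), then level of the intended first operator seniority". Every predictor named for imputation is therefore already in the analysis model. The singular form of the stratification variable does not change this, because age group and operator level are both there.

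On why data might be lost, the Sample size section assumes that "a proportion of patients enrolled will have a clinical deterioration, or other clinical events, during a high-stress procedure". It treats this as a possible obstacle both to giving the intervention and to recording the outcome, and allows 15% for both together. The Missing data section expects very few missing outcomes, because the paper form and the video both record them and the medical record is the fallback.

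**The concern.** A sensitivity analysis for missing outcomes is useful only if it can give a different answer when the primary analysis is biased. Here the imputed values are drawn from a relationship fitted to the observed encounters, using covariates on which the primary analysis already conditions. No new information enters, so agreement between the two analyses is built in.

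One of the plan's stated reasons for losing data, deterioration during the procedure, is plausibly related to hypoxaemia. If the 10% trigger were reached and loss depended on severity or on hypoxaemia itself, the primary estimate could be biased and the planned imputation would carry the same bias. A reader could then take the agreement as evidence of robustness when it shows nothing either way.

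**Working it through.** **The plan's own figures.** The inputs are 16% vs 8% hypoxaemia, 60% vs 80% first-attempt success, two-sided alpha 0.025, power 90% and 1:1 allocation (Sample size, Randomisation and Statistical principles sections). The per-arm formula with pooled variance is n = [z(0.9875)·√(2p̄q̄) + z(0.90)·√(p₁q₁ + p₂q₂)]² / (p₁ − p₂)².

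- Hypoxaemia: [2.2414·√0.2112 + 1.2816·√0.208]² / 0.0064 = 407.3, so 408 per arm and 816 in total.
- First-attempt success: [2.2414·√0.42 + 1.2816·√0.40]² / 0.04 = 128.04, so 129 per arm and 258 in total.
- Attrition: 816 / 0.85 = 960.

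All three match the SAP. The point concerns method, not a stated figure.

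**Why the two estimates coincide.** The complete-case logistic estimate θ̂ solves Σ xᵢ(yᵢ − pᵢ(θ̂)) = 0 over observed encounters. Imputed outcomes are drawn with mean close to pᵢ(θ̂), so the added terms Σ xᵢ(yᵢ* − pᵢ(θ̂)) over missing encounters average to about zero. The pooled analysis is therefore solved by about the same θ̂, plus noise from a finite number of imputations.

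**Simulation of the planned method.** There were 300 trials per mechanism, each with 960 encounters, 5 sites, 3 age groups, 2 operator levels and 10 imputations. Site was a fixed effect and no patient was re-enrolled. The effect of severity and the missingness mechanisms are assumptions. Entries are odds ratios for hypoxaemia.

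| Missingness depends on | Missing | Full data | Complete-case | Planned imputation | With severity added |
|---|---|---|---|---|---|
| Model covariates only | 16.8% | 0.489 | 0.481 | 0.483 | 0.484 |
| Severity, in the THRIVE arm only | 13.7% | 0.486 | 0.429 | 0.429 | 0.489 |
| The outcome, more strongly in THRIVE | 12.6% | 0.509 | 0.316 | 0.317 | 0.324 |

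The mean difference in log odds ratio, planned imputation minus complete-case, was 0.003, 0.000 and 0.002. Its SD was about 0.03 and the largest single difference was 0.105. Mean standard errors for complete-case and planned imputation were 0.224 and 0.226, 0.225 and 0.228, and 0.259 and 0.260. Bias against full data on the log scale was −0.125 for both methods in the second row, and −0.476 and −0.475 in the third. Adding severity removed the bias in the second row but hardly changed it in the third.

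**How far the bias depends on assumption.** A second set of simulations used 960 encounters, a standard normal severity score s, outcome logit −2.2 − 0.9·treatment + 1.2·s, missingness logit −2.3 + slope·s, and unadjusted odds ratios.

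| Slope, control / THRIVE | Full data | Complete-case |
|---|---|---|
| 1.3 / 1.3 (about 14% missing) | 0.45 | 0.44 |
| 1.3 / 0.26 | 0.46 | 0.55 |
| 0.26 / 1.3 | 0.45 | 0.36 |

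**Extreme bounds at the plan's rates.** Assume that all 15% attrition is missing outcomes, split equally: 480 per arm, 72 missing and 408 observed. Expected events are 0.16 × 408 ≈ 65 in control and 0.08 × 408 ≈ 33 in THRIVE.

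- Observed: (33/375) / (65/343) = 0.46.
- All missing controls hypoxaemic, no missing THRIVE: (33/447) / (137/343) = 0.18.
- The reverse: (105/375) / (65/415) = 1.79.

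These are outer limits, not a forecast. They show how much the planned imputation leaves unexamined.

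**The case against.** The strongest case against giving this much weight is that it may never arise. The outcome has three sources, and the Data monitoring section plans verification of primary-outcome items for every enrolled patient. The imputation runs only above 10% missing and cannot alter the primary estimate. This stands, and it makes the point a contingency. It does not make the method informative if the contingency occurs.

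Several stronger readings are tempting but not supported:

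- A reader might infer that the imputation must reproduce the complete-case result exactly. With ten imputations it does so only up to Monte Carlo error. The SAP says the model will include the named variables, not that it contains nothing else. If the chained equations also used the other primary outcome, and only one of the two were missing, some information could enter, but the SAP does not say so. The imputation list also omits the patient effect, which could move results slightly for re-enrolled patients without adding information about missing values.
- A reader might infer that 15% of outcomes are expected to be missing because of deterioration. The 15% also covers other clinical events and failure to deliver the intervention. Under intention-to-treat, encounters without delivery stay in the analysis.
- A reader might infer a definite bias of known direction. Nothing in the SAP indicates that missingness will differ by arm, and the simulated shifts appear, vanish or reverse according to that assumption.

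It is also fair to object that number of attempts, rescue oxygenation and intubation-related adverse events make doubtful auxiliaries. They come largely from the same form and video as SpO₂, so they may be lost with it. The fix allows for this.

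**Conclusion.** The point holds in a limited form. If only the outcome is missing and the imputation uses the predictors the SAP names, the planned analysis is expected to return the complete-case estimate up to Monte Carlo error (mean log odds ratio differences of 0.000 to 0.003). It would carry over any bias from severity-related or outcome-related missingness. This near-equality held under every mechanism simulated.

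The size of the bias itself cannot be stated from the document. Under the assumed mechanisms it ranges from negligible (0.45 vs 0.44) to material in either direction (0.46 to 0.55, 0.45 to 0.36), and it is larger where loss depends on the outcome itself (0.509 to 0.316). The consequence arises only if more than 10% of outcomes are missing after three sources. The change is worth making because it is cheap and because the plan would rely on this analysis precisely when missing data had become a problem.

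**What to change.** 1. Extend the imputation model with baseline variables already listed in Tables 1 and 2: pre-intubation SpO₂, intracardiac right-to-left shunt, indication for intubation, respiratory support before intubation, and location. Impute within arm so that their relation to the outcome may differ by treatment. State that both age group and operator level are included.
2. Use number of attempts, rescue oxygenation and intubation-related adverse events as auxiliaries only where they are recorded although SpO₂ is not.
3. Add a delta-adjusted (tipping-point) or best/worst-case analysis, varied separately by arm. This is needed because auxiliaries alone do little if missingness depends on the outcome itself (0.317 to 0.324, against 0.509 with full data).

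The cost is a few lines of SAP text, declared as a change after publication as the SAP requires, and slightly more analysis work. The baseline variables need no new data collection. With about 33 hypoxaemia events expected among 408 THRIVE encounters, the categories of indication and respiratory support should be collapsed in advance so that within-arm imputation remains stable.

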### Statistical principles

The primary analysis will be conducted based on the intention-to-treat principle. Specifically, each randomised intubation encounter will be analysed based on the allocated treatment group, independent of compliance with the treatment delivered.

A per-protocol analysis including all intubation attempts where a study therapy was commenced (regardless of whether it was the therapy that was randomised) will also be undertaken and reported in the supplementary material.

The unit of analysis for most outcomes is the intubation encounter. If patients are required to be intubated more than once, they can be re-enrolled and re-randomised, theoretically receiving different study interventions for each intubation attempt within a single admission. For secondary outcomes relating to admission (i.e. ventilator-free days, length of ICU and hospital stay and death), only those patients with one enrolment per admission will be included in the primary and per-protocol analyses.

Statistical tests will be two-sided applying a statistical significance level of 0.05, although the primary outcomes will be analysed at a level of 0.025 (applying Bonferroni’s correction). We will not apply a formal correction for multiple testing to any of the subgroup analyses, sensitivity analyses or to the secondary outcomes. We will ensure conclusions drawn as a result of analyses are interpreted with deference to multiple comparisons.

If there is more than 10% of data missing for the primary outcomes, a sensitivity analysis using multiple imputation will be undertaken.

Continuous variables will be assessed for normality; this will be undertaken using visual inspection of histograms and *Q*-*Q* plots.

Descriptive statistics will be used when summarising variables; frequencies (percentages) for discrete variables, mean and standard deviation (SD) for normally distributed continuous variables, or, if continuous variables are non-normally distributed, median with interquartile range (IQR).

Subgroup analyses will be executed regardless of any potential treatment effect on the primary or secondary outcomes in the main cohort.

Changes to the analysis plan by the investigators effective after the publication of this SAP will be declared as such.

The statistical analysis will be undertaken using StataSE version 17 (StataCorp Pty Ltd., College Station, TX).

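### Fixing the imputation at ten datasets lets a borderline multiple-imputation sensitivity result depend on the random seed; 100 datasets would largely remove this for computing time alone

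*SAP article*

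**What the plan says.** The trigger appears twice in the SAP article. Under Statistical principles: "If there is more than 10% of data missing for the primary outcomes, a sensitivity analysis using multiple imputation will be undertaken". Under Missing data: "multiple imputation will only be undertaken if > 10% of the primary outcome data is unavailable and reported as sensitivity analysis".

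The Missing data section then specifies the method. It uses fully conditional specification, and "the imputation model will include randomised treatment arm, study site and the stratification variable". The number of datasets is fixed: "Ten sets of imputed data will be created using the methods described for the primary outcome". The output is also stated: "A pooled common effect estimate and 95% confidence interval will be generated from the imputed datasets". No p-value, threshold or decision rule is attached to this analysis.

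Two other statements give context. Under Statistical principles, "the primary outcomes will be analysed at a level of 0.025 (applying Bonferroni’s correction"), while sensitivity analyses receive no formal multiplicity correction. Under Sample size, the total of 960 encounters is reached by "Allowing for 15% attrition", which the plan attributes partly to outcome data that cannot be collected. The Missing data section itself expects very few missing primary outcomes.

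**The concern.** The trigger and the number of datasets work against each other. Because nothing is imputed at 10% missing or less, the number ten applies only when missingness is already appreciable, which is when the noise from using a finite number of imputations is largest.

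That noise is not sampling error. It changes with the random seed on the same data and can be made as small as one likes by imputing more often. The purpose of the analysis is to show whether the primary result holds up under missing data. If its answer near a boundary depends partly on the seed, it serves that purpose less well in the borderline case, and part of any gap from the main analysis could be simulation noise.

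**Working it through.** **Inputs from the SAP.** Ten imputations and the 10% trigger (Missing data). Rates of 16% and 8%, 816 evaluable encounters, 90% power, type I error 0.025, 15% attrition and 960 in total (Sample size). Allocation 1:1 (Randomisation).

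**Assumption.** The document gives no fraction of missing information (FMI). It is taken as about equal to the share missing, since the imputation model names only arm, site and the stratification variable. The main range is 10% to 15%.

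**The plan's own figure.** With a pooled-variance comparison of two proportions, two-sided 0.025 (z = 2.241) and 90% power (z = 1.282):

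n per arm = [2.241 × √(2 × 0.12 × 0.88) + 1.282 × √(0.16 × 0.84 + 0.08 × 0.92)]² / 0.08² ≈ 407.3, rounded up to 408.

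So 816 in total, and 816 / 0.85 = 960. Both match the SAP.

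**Standard error of the log odds ratio**, 408 per arm:

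√[1/(408 × 0.16 × 0.84) + 1/(408 × 0.08 × 0.92)] = √(1/54.8 + 1/30.0) = 0.227.

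**Monte Carlo noise of the pooled estimate**, relative to its standard error: √(FMI/(m + 1)), where m is the number of imputations. The range for the odds ratio is 1.96 × that ratio × 0.227 on the log scale. The p-value range over seeds takes a true p of 0.05, so z = 1.960 ± 1.96 × ratio.

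| m | FMI | Monte Carlo SD / SE | 95% range, log OR | p over seeds, true p = 0.05 |
|---|---|---|---|---|
| 10 | 10% | 0.095 | ±0.042 | 0.032 to 0.076 |
| 10 | 15% | 0.117 | ±0.052 | 0.029 to 0.083 |
| 50 | 15% | 0.054 | ±0.024 | 0.039 to 0.064 |
| 100 | 10% | 0.031 | ±0.014 | – |
| 100 | 15% | 0.039 | ±0.017 | 0.042 to 0.060 |

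The alternative form √(FMI/m) gives 0.100 and 0.122 for ten imputations. The two forms differ only in whether FMI includes the finite-m variance.

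**Check by simulation.** One fixed borderline dataset of 480 per arm with a 16% control rate, outcomes missing completely at random, imputed within arm, 20,000 repeats with ten imputations. The SD of the pooled estimate was 0.099 of the SE at 10% missing and 0.121 at 15%. The SD of the z-statistic was larger, 0.113 and 0.146, because the between-imputation variance is itself noisy with ten datasets. The p-value ranges in the table are therefore somewhat too narrow for ten imputations.

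**Efficiency.** 1/(1 + FMI/m) with m = 10 is 0.990 at 10% and 0.985 at 15%.

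**Clear results.** At a true p of 0.01, z = 2.576, which is 0.616 from 1.960. That is more than four of the simulated SDs (0.146) at 15% missing, so the 95% interval would not change its message.

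**Near p = 0.025.** z = 2.241 ± 1.96 × 0.117 gives p from 0.014 to 0.044 at 15% missing, wholly below 0.05. The chance that z falls below 1.960 is about 0.8% with SD 0.117 (0.281/0.117 = 2.4 SDs) and about 3% with the simulated SD of 0.146.

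**The case against.** A reader might infer that results near the trial's 0.025 level could give intervals on either side of no effect. The documents do not support that. The planned interval is a 95% interval, which crosses no effect at p = 0.05, and a result truly at p = 0.025 would cross it only about 1% to 3% of the time. Nor is 0.025 stated as a threshold here: the SAP applies it to the primary outcomes and gives no decision rule for the imputed analysis. This part of the objection stands, and the crossing problem belongs near p = 0.05.

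Read by size and direction, the noise is small. It is about 5% either way in the odds ratio, against a sampling interval of exp(1.96 × 0.227) = 1.56-fold either way. This also stands and limits the weight of the point.

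The 15% figure may overstate missing outcomes. It covers undelivered intervention as well as uncollected data, and under intention to treat the former is not missing outcome data. With case report form, video and medical record as sources, the analysis may never run. That is fair: 15% is an upper planning figure. But the number ten operates only above 10% missing, so the 10% row of the table is already the low end of its use, given the FMI assumption.

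The documents imply no particular larger number, and setting the number equal to the percentage of incomplete cases would give only about 11 to 15. That is true. The case for 50 to 100 rests on the size of the noise in the table. The absence of a stated seed is a programming detail in a condensed article and is not held against the plan.

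**Conclusion.** The point holds as a small one about reproducibility. With ten imputations, and assuming FMI about equal to a 10% to 15% share missing, the pooled estimate carries avoidable noise of 0.10 to 0.12 of its standard error, about three times that with 100.

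Neither the validity nor the efficiency of the analysis is affected, and the primary test is untouched. The consequence is confined to borderline results. Close to p = 0.05 the planned 95% interval can include or exclude no effect depending on the seed.

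The same noise would matter near 0.025 only if someone chose to read the result against the primary-outcome level, which the Missing data section does not state. On that reading, a true p of 0.020 at FMI 15% would land on the wrong side of 0.025 about 24% of the time with ten imputations, 6% with 50 and 1.4% with 100.

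**What to change.** In the Missing data section, replace ten by 100 imputed datasets (at least 50), and state that the Monte Carlo error of the pooled log odds ratio will be reported with the pooled estimate and its interval. The trigger, the imputation model and the status as a sensitivity analysis need not change for this point. The cost is one number, one sentence and extra computing time.

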#### Additional analyses

Analyses that have not been pre-defined in the protocol may be performed if requested by journal editors or reviewers. Any such analysis will be performed in a manner consistent with this analysis plan where possible. Subsequent exploratory analyses of the dataset following the publication of the main outcomes paper will not be bound by this strategy but will follow the broad principles we describe here.

